## Abstract

**Background:**

Protected areas are crucial for the maintenance of human health and well-being. They aim to preserve biodiversity and natural resources to secure various ecosystem services that are beneficial to human health. Their ecological characteristics can influence local health literacy. Typically, communities surrounding protected areas have limited economic opportunities due to restriction policies to protect the ecosystem, resulting in socioeconomic disparities. The local community faces obstacles in gaining access to health care facilities and health information due to these limitations. It is difficult for them to locate, comprehend, and apply information and services to make better health-related decisions for themselves and others.

**Objective:**

This study protocol examines the impact of the ecosystem on health literacy among rural communities in protected areas.

**Methods:**

This study comprises 5 phases. In phase 1, we conduct a systematic review to identify the issue of health literacy in protected areas. In phase 2, we will collect data from stakeholders in a protected area of Pahang National Park and analyze the results using Net-Map analysis. In phase 3, we will conduct a survey among the adult community in Pahang National Park related to health literacy, socioeconomic status, health expenditure, and quality of life. In phase 4, informed by the results of the survey, we will determine suitable intervention programs to improve health literacy through a focus group discussion. Finally, in phase 5, we will conduct a costing analysis to analyze which intervention program is the most cost-effective.

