Based on the available evidence, this study aims to (1) conduct a systematic review to understand the health literacy status among rural communities surrounding protected areas; (2) explore stakeholders’ perceptions of health literacy status among rural communities surrounding protected areas; (3) determine the health literacy status and its associated factors among rural communities located near protected areas; (4) develop a new health literacy intervention program for rural communities near protected areas; and (5) conduct a cost structure analysis of the new health literacy intervention programs for rural communities surrounding protected areas.

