### Phase 5: Conducting a Cost Structure Analysis of the New Health Literacy Intervention Programs for Rural Communities Surrounding the Protected Area

#### Overview

Phase 5 is a continuation of Phase 4. We will conduct a cost analysis for every intervention program listed in Phase 4.

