#### Data Collection Procedure

The cost structure will be prepared based on advice from experienced agencies or individuals in the field. A list of intervention activities will be presented as an alternative to the policy makers or any agencies who are interested in improving health literacy among the PNP community.

Economic data on providers' costs will be collected for the financial year 2021 to 2022. The data obtained will contain information on the costs incurred at the intervention and funding agency levels. When valuing economic costs, the opportunity cost of each resource will be considered, encompassing all resources used in the intervention, including those that are donated or subsidized. This approach ensures a uniform method of data collection, enabling reliable cost comparisons among the various interventions.

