#### Data Analysis Procedure

The cost analysis will analyze expenses based on the cost unit, source data, and frequency, with comparisons made across the intervention programs. The cost unit pertains to the expenses associated with each intervention per patient per year. Simultaneously, the sources of data serve as evidence for the interventions, and frequency refers to the number of interventions required annually.

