## Results

The project was funded by USIMl and strategic research partnership grants. Enrollment for the overall project is ongoing. We are conducting a systematic review of health literacy in protected areas and conducting a cross-sectional study based on the survey results to determine the determinants of health literacy in protected areas. Findings from this study will be used to develop a sustainable health intervention module with an effective cost that may be adopted in all protected areas in Malaysia. The first results are expected to be submitted for publication in 2024.

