### Strengths and Limitations

This study’s strength lies in its mixed methods analysis, employing a triangulation process to converge and validate both qualitative and quantitative data [27]. Moreover, this study will be conducted in multiple phases to discuss the issue comprehensively. This structured approach facilitates incremental progress [28]. Phases 1 and 2 are conceptual phases where the issue is identified and validated through a systematic review by stakeholders in PNP, such as government agencies, knowledge institutions, and civil society organizations. Phase 3 will design and plan the questionnaire and examine the health literacy status and its influencing factors among the community. The stakeholders in the FGD in phase 4 will validate the results of phases 1 to 3. Using these results, the stakeholders will discuss and design an effective health literacy intervention program. Finally, phase 5 will involve the dissemination of the health literacy intervention program to improve the health literacy status in the community. Moreover, a cost analysis will be calculated to analyze the cost of the program.

The study’s limitations became apparent during the FGD session with the stakeholders, as the invited participants did not attend. Consequently, we missed capturing unique macro-level perspectives. Another limitation is that the stakeholders’ views may not be representative of all who live inside or near the protected area in Malaysia or globally. Additionally, the study did not address the distinctions between locals and outsiders. Access to rural areas is difficult logistically, and the potential presence of wildlife, such as tigers, elephants, and bears, further complicates the research process.

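### The abstract says Phase 5 will show which programme is most cost-effective, but the planned data are costs only and cannot support that conclusion

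*Protocol article*

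**What the plan says.** The Methods paragraph of the abstract describes the last phase this way: "we will conduct a costing analysis to analyze which intervention program is the most cost-effective".

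The body of the article describes it differently:

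- Aim 5 in the Introduction is to "conduct a cost structure analysis of the new health literacy intervention programs for rural communities surrounding protected areas".
- Phase 5, Overview: "We will conduct a cost analysis for every intervention program listed in Phase 4".
- Phase 5, Data Collection Procedure: "Economic data on providers' costs will be collected for the financial year 2021 to 2022". These are costs at the level of the intervention and of the funding agency, valued at opportunity cost. A list of activities then goes to policy makers and other interested agencies as alternatives.
- Phase 5, Data Analysis Procedure, states: "The cost analysis will analyze expenses based on the cost unit, source data, and frequency, with comparisons made across the intervention programs". Cost is expressed as the annual expense of an intervention per patient, and frequency is the number of interventions needed in a year.

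The Conclusions paragraph of the abstract, the account of the cost analysis under Strengths and Limitations, and the closing Conclusions section also speak of cost or cost structure only.

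**The concern.** To call one programme the most cost-effective of several is a comparative statement that needs two quantities for each programme: what it costs and what it achieves. The Phase 5 methods supply the first. If the second is supplied nowhere, the abstract announces a conclusion that the study cannot reach.

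This matters beyond wording. The list of programmes is meant for policy makers and agencies, and the Results section foresees adoption in all protected areas in Malaysia. Readers who take the abstract at its word would expect a ranking by value for money, whereas the data can give only a comparison of expense.

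**Working it through.** **Step 1: look for an effect in each phase.** The article gives no cost, effect or cost-effectiveness figure for any programme, so there is no stated figure to reproduce. The check is whether any phase produces an effect input.

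| Phase | What it yields | Quantitative programme effect? |
|---|---|---|
| 1 | Systematic review of health literacy status, synthesised by thematic coding | No; no extraction of effect estimates is described |
| 2 | Stakeholder perceptions and Net-Map thematic analysis | No |
| 3 | Cross-sectional survey of health literacy, expenditure and quality of life, done before the programmes are chosen | No; scores are tied to no programme and no repeat measurement is described |
| 4 | Programmes proposed from stakeholder and expert opinion, set out in a logical framework (Table 5) | No; the goal and purpose rows mention benefits and desired change, but ask for no size, measure or source |
| 5 | Provider and funding-agency costs, expense per patient per year, frequency | No; the denominator is persons, not outcome gained |

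The nearest wording to an effect input is the statement in the Phase 5 Data Analysis Procedure that data sources act as evidence for the interventions. It is ambiguous, but it names no outcome, no effect size and no source of one.

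**Step 2: what a cost comparison can show.** For programmes A and B, with cost per person C and effect per person E, the cost per unit of effect is C/E. Write k = C_B/C_A (greater than 1, so B is dearer) and r = E_B/E_A. Then

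(C_B/E_B) ÷ (C_A/E_A) = k/r.

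B is the more cost-effective programme when r > k, A when r < k, and they tie when r = k. Costs give k. Nothing planned gives r.

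**Step 3: illustration on assumed values.** None of these figures comes from the article. Let A cost 100 units per person and raise the proportion with adequate health literacy by 5 percentage points, so 100/0.05 = 2,000 per additional adult with adequate literacy.

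| k | r | B: cost per additional adequate adult | More cost-effective |
|---|---|---|---|
| 1.5 | 1.25 | 150/0.0625 = 2,400 | A |
| 1.5 | 1.5 | 150/0.075 = 2,000 | tie |
| 1.5 | 2 | 150/0.10 = 1,500 | B |
| 2 | 1.5 | 200/0.075 = 2,667 | A |
| 2 | 2 | 200/0.10 = 2,000 | tie |
| 2 | 3 | 200/0.15 = 1,333 | B |

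A is cheaper in every row, yet the answer depends on r. Under equal effects (r = 1) the cheapest programme would also be the most cost-effective, but the article neither states nor tests that condition.

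**The case against.** **The working plan is coherent.** The strongest reply is that the aim, the Phase 5 heading, its methods and the closing sections all promise a cost analysis and describe one. The claim of greatest cost-effectiveness appears only in the abstract. This stands, and it lowers the severity: the fault is an abstract that overclaims, not a cost analysis that is wrong for its own objective.

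**The article condenses a fuller protocol, which may say what the evidence for the interventions is.** This carries less weight. The article does describe the data and analysis of Phase 5, and both are cost-only. The point is that a stated conclusion does not follow from the stated method, not that detail is missing.

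**Effects are not wholly absent.** Phase 4 participants are to discuss which measures would be effective, and Table 5 mentions benefits and behaviour change. That is true, but these are qualitative and cannot enter a ratio.

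**A stronger reading to avoid.** A reader might infer that the study will offer policy makers the cheapest programme as the most cost-effective one. The article does not say so. It plans comparisons of expense without a decision rule, and it presents a list of alternatives rather than one chosen programme.

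**Two other phrases.** Likewise, "Findings from this study will be used to develop a sustainable health intervention module with an effective cost" does not claim to identify the most cost-effective programme, and "phase 5 will involve the dissemination of the health literacy intervention program to improve the health literacy status in the community" states the purpose of dissemination, not a measured result. Neither is needed for the point.

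**Conclusion.** The point holds in a limited form. The abstract states a conclusion about cost-effectiveness that the planned data cannot support: each quantity specified for the Phase 5 comparison is a cost or a count, no phase provides a quantitative programme effect, and equal effects are not assumed. A comparison of costs alone cannot settle which programme is most cost-effective.

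The size of any misranking is unknown. The condition r > k is general, but the figures that illustrate it are assumed and say nothing about how likely a reversal is at this site. Severity is moderate: the overclaim is confined to one sentence of the abstract, but it changes what Phase 5 may be said to conclude.

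**What to change.** **Preferred.** In the Methods paragraph of the abstract, replace the clause on the most cost-effective programme with wording such as: *in phase 5, we will carry out a cost analysis and compare the cost per participant per year of each intervention programme.* This matches aim 5, the Phase 5 methods and the abstract's own Conclusions. Draw no cost-effectiveness conclusion from Phase 5 when it is reported. The cost is one sentence, with no new data and no new participants.

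**Only if a cost-effectiveness conclusion is wanted.** For each programme, state an expected change in the proportion with adequate health literacy, its source, and a low, base and high value. Report cost per additional adult with adequate literacy over that range, labelled as modelled. This costs one extra entry per programme and a small sensitivity table. The downside is that the inputs would be uncertain: Phase 1 is scoped to health literacy status rather than programme effects, and stakeholder estimates would be opinion.

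**Optional.** Tidy the looser phrases in the Results section and under Strengths and Limitations so that they speak of cost and of dissemination only.

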**Results:**

This study was funded by Universiti Sains Islam Malaysia (USIM) and strategic research partnership grants, and enrollment is ongoing. The first results are expected to be submitted for publication in 2024.

**Conclusions:**

This is one of the first studies to explore health literacy among rural communities in protected areas and will provide the first insights into the overall level of health literacy in the protected community, potential determinants, and a suitable intervention program with expected cost analysis. The results can be used to promote health literacy in other protected areas and populations.

**Trial Registration:**

International Standard Randomized Controlled Trial Number Registry ISRCTN40626062; http://tinyurl.com/4kjxuwk5

**International Registered Report Identifier (IRRID):**

PRR1-10.2196/51851

## Introduction

Good health and well-being can be achieved with adequate health literacy [1,2]. Adequate health literacy indicates that the individual can obtain, process, understand, and apply basic health information and services needed to make appropriate health decisions [3]. Higher levels of health literacy allow people to make better health decisions [4], be more committed, and do their jobs more efficiently [5]. Patients must have enough information about their health to leverage it and make well-informed decisions regarding getting health treatments and medicine. In the context of preventive health care, an adequate level of health literacy helps ensure that patients get the most out of their health investments and make the best use of resources [6]. According to the World Health Organization (WHO), people residing in rural areas often experience socioeconomic inequity and lower educational attainment due to imperfect living conditions. These areas are cut off from urban centers and have limited facilities [7,8]. The varying ecosystems within the population may influence different levels of health literacy.

People living in the protected areas often have limited health literacy [9]. The government designates protected areas for conservation purposes. Thus, less emphasis is placed on new land development for farming, housing, and infrastructure [10-12]. As a result, populations encounter challenges in gaining better access to networks, health facilities, the internet, and other resources. This limitation, in turn, adversely affects their quality of life [9]. The health outcomes, living conditions, and education levels of the population residing in rural areas lag significantly behind those living near urban centers. This disparity places people in rural areas at a disadvantage when it comes to making informed health decisions, as they have limited knowledge in this regard.

Accordingly, policy makers are putting in place and advocating for health programs and awareness campaigns to improve the health literacy status among populations in rural and protected areas [13]. However, this strategy is hard to implement in communities that live in protected areas as they have limited educational backgrounds. They struggle to access, obtain, understand, and apply health information in their daily lives. Moreover, they are often unable to access health information when they are sick. Indigenous people often turn to traditional remedies, consult shamans, or opt for inaction with the hopes that the illness will recover on its own [14]. The limited knowledge of hygiene among indigenous people has prompted the government to develop a specialized syllabus for indigenous children at primary school. This curriculum focuses on teaching essential practices, such as washing hands, proper toilet usage, and dental hygiene. Understanding the impact of protected areas on health literacy in local communities is crucial to sustaining their way of life and health. However, the level of health literacy and its response to protected areas varies, depending on factors such as the type of protected area, how policies are planned, and how they are implemented [15].

Research on health literacy among people who live in protected areas is important for understanding their needs for access to health care, disease prevention, health promotion, and health care. It will also help elucidate how to meet these needs in the best and most effective way. Nevertheless, thus far, there has been limited research on health literacy and health issues among people in protected areas considering 4 perspectives (ie, that of government entities, knowledge institutions, civil agencies, and local communities). Accordingly, this paper proposes a study that will examine health literacy and health status of communities in protected areas. The study protocol can serve as a model for similar investigations in protected areas in other countries.

Based on the available evidence, this study aims to (1) conduct a systematic review to understand the health literacy status among rural communities surrounding protected areas; (2) explore stakeholders’ perceptions of health literacy status among rural communities surrounding protected areas; (3) determine the health literacy status and its associated factors among rural communities located near protected areas; (4) develop a new health literacy intervention program for rural communities near protected areas; and (5) conduct a cost structure analysis of the new health literacy intervention programs for rural communities surrounding protected areas.

## Methods

### Background and Conceptual Model

This study adopts a mixed methods approach to investigate health literacy.

Our understanding of health literacy is underpinned by the four core dimensions of the Health Literacy Model [16]: (1) accessing, (2) understanding, (3) appraising, and (4) applying health information. Based on this model, this study will explore the impact of the ecosystem on health literacy among rural communities in protected areas. Figure 1 explains the conceptual model for this study.

**Figure 1 figure1:**
[figure not shown]
Conceptual model of the study.

### Study Site

This study comprises one of Malaysia's protected areas, Pahang National Park (PNP). There are 53 national and state parks in Malaysia, with PNP being among the country’s most important and best-protected conservation areas. The region has diverse populations, including Malay and indigenous communities. As per the Jabatan Kemajuan Orang Asli (JAKOA; translated to Department of Orang Asli Development) [17], Pahang has the highest number of indigenous communities (37.9%) in Malaysia. Because the PNP site fulfills the criteria for this research (ie, the implementation of a protected area and the presence of legal or other formal mechanisms promoting such an area), we selected it as our study area.

### Research Design

This study contains 5 phases consisting of identifying the health literacy issues in this area, confirming the issues, testing the issues, and preventing and analyzing the issues. The 5 phases will be carried out based on the 5 objectives.

### Phase 1: Identifying Issues Through a Systematic Review

#### Overview

In phase 1, we will review the literature to understand the health literacy status among rural communities surrounding protected areas. This phase will involve conducting a systematic review following the PRISMA (Preferred Reporting Items for Systematic Reviews and Meta-Analyses) guidelines.

#### Approach

The systematic review will use a standard search string using the PICO (Population, Intervention, Comparison, and Outcome) structure. For the keyword search, we will use PubMed, Scopus, and Web of Science databases. Later, 2 reviewers will be appointed to appraise all selected studies. The result will compile the highest quality studies relevant to the study objectives.

#### Eligibility

The selection of results will be based on the following eligibility criteria: (1) full articles written in English and (2) articles published between 2012 and 2022. The exclusion criteria include (1) gray literature and (2) articles outside the scope of our research. The screening process will consider the qualifying requirements established.

#### Quality Assessment

First, 2 reviewers will conduct a quality assessment using a set of study quality assessments checklist. The checklist consists of eight evaluation criteria: (1) research goals, (2) study design, (3) study outcomes, (4) sample size calculations, (5) analysis of findings, (6) variance estimates for the primary results, (7) adequate reported results, and (8) conclusions. A quality score is one way to incorporate quality into the review process [18]. The reviewers will assign 2 points to articles that meet all criteria, 1 point if they fulfill some requirements, and 0 points if they do not. Subsequently, the quality score will be calculated by aggregating all elements from the quality assessment tool to provide an overall single score. In case of disagreements, a third reviewer will be appointed.

#### Data Coding and Analysis

This study employs a thematic synthesis, utilizing a 2-step coding procedure wherein reviewers will code each line of text from the articles separately for its meaning and substance. Before finishing this step, we will analyze every text associated with a particular code to ensure that the interpretation is consistent.

